## 3.3 Justification of Dose and Dosing Regimen

Dose selection was based on the following considerations to prior clinical experience with AXA1125, AA modality, formulation feasibility, subject compliance, and PK.

- The nonclinical safety of individually administered constituent AAs of AXA1125 has been well described in the literature. At the highest planned dose of 67.8 g/day AXA1125 (33.9 g BID), the doses of constituent AAs (ie, leucine 12 g, isoleucine 6 g, valine 6 g, arginine 18 g, glutamine 24 g, and Nac 1.8 g) are all below the corresponding HED values, calculated from published NOAEL values as adjusted for a 60-kg individual. In these nonclinical studies, when AA constituents were administered individually at doses 2 to 4 times higher than the NOAELs, AEs (when present) were generally mild, transient, and monitorable (see Section 1.4.2).
- The safety and tolerability of the highest dose of 67.8 g/day is supported by the Studies AXA1125-001 and AXA1125-002. Even at the highest dose of 67.8 g/day, AEs observed to date have been primarily mild to moderate gastrointestinal findings (diarrhea, abdominal pain, or discomfort), which are typically self-limited (see Section 1.5.2.1).
- Based on PK observations, the doses up to 33.9 g BID (67.8 g/day) are expected to deliver key AAs in the systemic circulation in the linear AUC range. Similar to Study AXA1125-003, which showed encouraging biological activity, a BID regimen was chosen for Study AXA1125-101 to ensure optimal subject compliance during chronic dosing.
- AXA1125 can be administered with or without food based on the preliminary PK data.
- Daily administration of AXA1125 at 22.6 g TID (67.8 g/day) up to 12 weeks (Study AXA1125‑002) or 22.6 g BID (45.2 g/day) up to 16 weeks (Study AXA1125‑003) was associated with clinically relevant changes in biomarkers of metabolism and fibroinflammation (eg, MRI-PDFF, Pro-C3, and ALT) in subjects with NASH.
- Pharmaceutical properties were also considered. A single sachet is designed to deliver 11.3 g of AXA1125 AAs. The excipients and their respective concentrations were specifically chosen for AXA1125 and were designed to deliver a uniformly dispersed, orange-colored, orange-flavored liquid suspension upon constitution of up to 3 sachets (33.9 g of AXA1125 AAs) in ~6 fluid oz (~180 mL) of potable water. Specifically, the concentration of lecithin ensures sufficient wetting of the hydrophobic AAs (eg, leucine, isoleucine, and valine) to deliver a uniform dispersion of these ingredients in the 6 fluid oz dose volume. The concentration of xanthan gum has been titrated to the 6 fluid oz dose volume to create the required liquid suspension presentation. Finally, the citric acid and orange-flavor concentrations were chosen to deliver a pleasant orange-colored, orange-flavored drink in the 6 fluid oz dose volume. These excipients in combination with other nonactive ingredients in the drug product enable the delivery of positive organoleptic properties (eg, acceptable mouthfeel and taste) to subjects, potentially aiding in subject dose administration compliance. Therefore, doses >33.9 g (ie, 45.2 g) warrant a higher volume (>6 fluid oz) of potable water for constitution, which could negatively impact subject compliance, palatability, and tolerability. Also, to maintain study blinding, AXA1125 or placebo will be delivered in the same 6 fluid oz dose volume. Using a higher volume for the active arm but not the placebo arm could potentially unblind the study. Similarly, the use of 33.9 g TID also poses blinding and compliance issues.
- Unlike 2 doses studied in NASH, a single dose of 33.9 g BID is proposed for the PASC study. While the ongoing NASH study provides dose-response information on several biomarkers, the use of a single dose (33.9 g BID) in PASC allows for maximizing Nac dose (1.2 g BID) and thereby maximizing intracellular glutathione pools that have been considered crucial for ameliorating COVID-19-related mitochondrial dysfunction. Furthermore, 10 g TID glutamine (30 g/day) supplementation in subjects with COVID-19 has been shown to shorten the length of hospital stay and reduce the need for intensive care unit treatment (Cengiz 2020). The 33.9 g BID AXA1125 dose also allows for maximizing glutamine dose at 12 g BID (24 g/day).

Overall, the available PK and PD data along with considerations related to formulation feasibility, available clinical safety data, biologically relevant concentrations, and literature support the selection of 33.9 g BID (67.8 g/day) as an adequate dose to evaluate the safety and tolerability of AXA1125 in subjects with PASC in Study AXA1125-201.

## 3.4 Study Duration

**Cohort A**

Subjects will participate for up to 9 weeks. The study will comprise a Screening Period of up to 4 weeks, a Treatment Period of 4 weeks, and a Follow-up Period of 1 week. **Cohort B**

The total study duration for each subject in Cohort B will be approximately 6 weeks, which will comprise a Screening Period (1 week), Baseline Visit, a Treatment Period of 4 weeks, and a Followup Period of 1 week.

# 4 STUDY POPULATION AND SELECTION

## 4.1 Inclusion Criteria

A subject must meet all of the following inclusion criteria to be considered for enrollment into this study:

###### Cohort A and B

1. A subject must be male or female 18 years of age or older, and under 65 years of age.
2. A subject must be able to provide written informed consent and be able to understand and willing to comply with specified requirements as stated in the protocol.
3. A subject must have had clinically suspected COVID-19 and a positive antibody test or a documented SARS-CoV-2 infection (a positive reverse transcription polymerase chain reaction test) at least12 weeks prior to Screening.

Note: Subjects who had a clinical diagnosis of COVID-19, but could not have a PCR test due to the need to self-isolate are allowed.

1. A subject must have fatigue-predominant PASC defined by:

###### Cohort A Only

• an elevated PCr recovery rate constant following moderate exercise on 31P-MRS (τ_PCr_ ≥50 seconds); and

Note: Documented 31P-MRS within 3 months of Screening and after 3 months of acute COVID-19 infection is acceptable. If a historical 31P-MRS has been used to determine eligibility, then 31P-MRS should be repeated within 1 month prior to Day 1 (ie, during the Screening Period) to confirm eligibility and establish baseline.

1. Other than PASC, a subject must be in good health without other significant medical or not well controlled medical or psychiatric conditions. Allowable conditions include mild hypertension,

dyslipidemia, pre-diabetes defined as HbA1c ≤ 6.0%, and/or asthma (mild and not requiring chronic daily treatment). Subjects who are treated for these conditions must be well controlled on a stable regimen (lifestyle modifications and/or medications), for at least 3 months prior to Screening and anticipate no significant alterations to these regimens for the duration of the study. However, doses of certain medications (eg, statins, antihypertensives) used to treat stable chronic conditions may be modified during the study for safety or tolerability issues, if needed at the discretion of the Principal Investigator (PI).

Note: A history of treated hepatitis C virus (HCV) infection is allowed, provided that a negative hepatitis C viral load has been documented at ≥12 weeks after the cessation of hepatitis C treatment. Historical medical record or testing to ensure a negative viral load may be permitted during the Screening Period. HCV ribonucleic acid will be tested in all subjects, including subjects with a history of treated HCV infection or with positive HCV antibody at Screening, provided that a negative hepatitis C viral load has not been documented at ≥12 weeks after the cessation of hepatitis C treatment.

1. A female subject must meet any one of the following criteria:
   1. Surgically sterile
   2. Postmenopausal with ≥12 months of amenorrhea without an alternate medical cause
   3. Follicle-stimulating hormone (FSH) level consistent with postmenopausal state if amenorrheic for <12 months or if <55 years of age
   4. If a subject is of childbearing potential, must have a negative serum pregnancy test during Screening and agree to abstain from sexual activity or agree to use a highly effective form of birth control (failure rate <1% per year) for the duration of the study and for at least 30 days after the last dose of study drug
2. A male subject must meet the following criteria:
   1. Male subjects with a partner who is a female of childbearing potential (FCBP), must agree to abstain from sexual activity or agree to use a highly effective form of birth control (failure rate <1% per year) for the duration of the study and for at least 90 days after the last dose of study drug. Note: Female partner use of a highly effective form of birth control (failure rate <1%) is acceptable for male subjects participating in the study.
   2. Male subjects capable of fathering a child must agree to refrain from sperm donation for the duration of the study and for at least 90 days after the last dose of study drug.
3. A subject must agree to refrain from physical activity outside of normal activities of daily living before Day 1 and for the duration of the study
4. A baseline CFQ-11 total fatigue score (by Bimodal Scoring) of ≥8.

## 4.2 Exclusion Criteria (Cohort A and B)

A subject will be excluded from the study if **any** of the following criteria are met:

1. Other than PASC, have an explanation for fatigue. This includes but is not limited to hypothyroidism; chronic cardiovascular, neurological, endocrinological, or peripheral vascular disease; history of major depression; clinically significant anemia; chronic liver disease; rheumatologic diseases requiring treatment with steroids or immunosuppressants; or other cause of neuromuscular disease such as muscular dystrophy.
2. Other than PASC, a history or presence of an uncontrolled, clinically significant disease including:
   - Type 1 or Type 2 diabetes mellitus
   - A medical condition that may interfere with absorption of the study drug, including but not limited to resection of any part of the gastrointestinal tract, gastric or intestinal bypass, any bariatric surgery, or inflammatory bowel disease
3. Meet any of the following during physical exam assessment:
   - Resting O_2_ saturation <95% on room air
   - Body mass index (BMI) of <18.5 or >35
   - Clinically significant abnormality on echocardiogram (to rule out abnormal cardiac function or elevated pulmonary artery pressure)
   - Is pregnant (if female) or lactating
4. Meet any of the following laboratory parameters:
   - Serum B-type natriuretic peptide (NT-proBNP) >400 pg/mL
   - Total bilirubin >1.3 mg/dL (>22.23 umol/L) or direct bilirubin >0.40 mg/dL (>6.84 umol/L) unless with a history of Gilbert’s syndrome
   - Aspartate aminotransferase (AST) or ALT >3 × upper limit of normal (ULN) AST >126 IU/L; ALT >135 IU/L
   - HbA1c >6.0%
   - Human immunodeficiency virus (HIV)-1 or -2 positive
   - eGFR <60 mL/min/1.73 m2 calculated using the Chronic Kidney Disease Epidemiology Collaboration equation
   - Positive for hepatitis B surface antigen (hBsAg), HCV antibody, or HIV antibody
5. Have a medical history that includes any of the following:
   - Non-invasive or invasive ventilatory support for COVID-19
   - Intensive care unit or other high dependency unit admission for COVID-19
   - Hospitalization for >1 week for COVID-19 without intubation
   - Planned or prior organ transplant
6. Treatment with drugs known to cause myopathy in the last 3 months. This includes glucocorticoids, antimalarials, colchicine, antiretroviral drugs, interferon alpha, penicillamine, immune checkpoint inhibitors, tumor necrosis factor inhibitors and statins, if there is a history of statin-induced muscle pain.

Note: The Medical Monitor should be consulted if there are questions regarding concomitant medications.

1. Unwilling or unable to stop the use of AA or protein supplements, carnitine, creatine, or Nac at the time of Screening until the end of study
2. A history of inborn errors of metabolism that may impact AA metabolism, including but not limited to urea cycle disorders
3. A contraindication for a safe magnetic resonance imaging scan, including implanted magnetic metal
4. Any history of illicit drug or alcohol abuse within 6 months prior to Screening.
5. Used an investigational drug, product, or device within 30 days or 5 half-lives (whichever is longer) before Screening, or is enrolled in another investigational drug, product, or device study within 30 days before Screening; Note: Enrollment in registration or observational studies is permitted.
6. A contraindication, sensitivity, or known allergy to any ingredient of AXA1125; or
7. Considered, in the opinion of the PI, to be a poor attendee, or for any reason is not able to comply with the study procedures due to reasons such as planned procedures, travel, etc, that would occur during the course of the study

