# 5 STUDY INTERVENTIONS (Cohort A and B)

## 5.1 Study Drug

### 5.1.1 AXA1125

AXA1125 is an orally active mixture of 5 specific AAs (leucine, isoleucine, valine, arginine, and glutamine) and Nac (an AA derivative). The AA composition within AXA1125 is described in Table 1.

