###### Table 1 Amino Acid Composition Within AXA1125

| **Ingredient** | **Ingredient Function** | **Unit Dosage Dry Weight (g)** |
| --- | --- | --- |
| L-Leucine | Active | 2.000 |
| L-Isoleucine | Active | 1.000 |
| L-Valine | Active | 1.000 |
| L-Arginine HCl^1^ | Active | 3.628 |
| L-Glutamine | Active | 4.000 |
| N-acetyl-L-cysteine | Active | 0.300 |

HCl=hydrochloride

Note: Total may be >100% due to rounding off.

^1^ Arginine is sourced as arginine monohydrochloride; 3.628 g of L-Arginine HCl equals 3.001 g of L-Arginine.

The excipients within AXA1125 include citric acid, soybean lecithin, xanthan gum 180, sucralose, orange flavor, custard flavor, FD&C yellow no. 6, low-substituted hydroxypropyl cellulose NBD-022, colloidal silicon dioxide, magnesium stearate, and AAs without hydrochloride. The excipients and their respective concentrations were specifically chosen for AXA1125 and are designed to deliver a uniformly dispersed, orange-colored, and orange-flavored liquid suspension upon constitution with ~6 fluid oz of potable water.

The active pharmaceutical ingredients and excipients are compounded to produce a uniform dry powder blend for suspension and are provided as a unit dose sachet containing 11.3 g AAs. The container closure system for AXA1125 is a 5-layer

(paper/polyester/polyethylene/foil/polyethylene), heat-sealed, unit-dose, foil sachet. One end of the heat-sealed sachet is notched to provide an easy-tear opening for subjects.

Detailed information regarding AXA1125 formulation, constitution instructions, appearance, and storage requirements are described in the Pharmacy Manual.

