### 5.1.2 Placebo

The placebo is formulated as a dry powder that has excipient and calorie content similar to AXA1125 (see Table 2). Excipient content that is dissimilar to AXA1125 is as follows: soybean lecithin has been removed because it is not required to ensure sufficient wetting of the excipients in the placebo formulation, sodium citrate dihydrate has been added and the citric acid amount reduced in order to match the pH of AXA1125, and maltodextrin and sunflower oil powder have been added as fillers. Each placebo and AXA1125 sachet contain approximately 76 kcal and provide approximately 456 kcal/day to subjects regardless of the treatment arm.

The placebo will be supplied to closely match the aroma, appearance, color, and taste profile of AXA1125 as powder in sachets. The total number of sachets, packaging, constitution, and administration of placebo mirrors AXA1125 to maintain double blinding during the study.

Calories are primarily delivered by a combination of maltodextrin (~50.4 kcal per sachet, or up to 302 kcal per day based on 3.78 kcal/g) and sunflower oil powder (~21.5 kcal per sachet, or up to 129 kcal per day based on 7.38 kcal/g). In Study AXA1125-003, the additional calories delivered to the subjects receiving placebo with similar composition did not result in an increase in weight, HbA1c, fasting glucose, or the AUC of glucose in an oral glucose tolerance test from baseline to Week 16 (see the current version of the IB); assessments of weight and glucose homeostasis are included in this study.

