###### Table 2 Excipient Function Within Placebo

| **Ingredient** | **Ingredient Function** |
| --- | --- |
| Maltodextrin, NF | Filler |
| Sunflower oil powder | Filler |
| Citric acid, anhydrous | pH adjuster |
| Sodium citrate, dihydrate,^1^ NF | Buffer, pH adjuster |
| Xanthan gum 180 | Thickening agent |
| Sucralose, powder | Sweetener |
| Orange flavor, natural and WONF | Flavor |
| Custard flavor, natural and artificial | Flavor |
| FD&C yellow no. 6 | Color |
| Low-substituted hydroxypropyl cellulose NBD-022 | Disintegrant |
| Colloidal silicon dioxide | Disintegrant |
| Magnesium stearate | Lubricant |

FD&C = food, drug, and cosmetic; NBD = New Binder Disintegrant; NF = National Formulary; WONF = with other natural flavors.

^1^ The total citric acid amount is distributed between citric acid and sodium citrate to ensure target pH. Total daily amount of citric acid matches the total daily amount in AXA1125.

Detailed information regarding the placebo formulation, constitution instructions, appearance, and storage requirements are described in the Pharmacy Manual.

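### The allergy exclusion names only ingredients of AXA1125, so a known allergy to a placebo-only ingredient is not explicitly excluded

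*Protocol*

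**What the plan says.** The allergy criterion has the same wording in the Protocol synopsis and in Section 4.2. It excludes a subject with "A contraindication, sensitivity, or known allergy to any ingredient of AXA1125" and does not mention placebo.

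Section 5.1.1 describes AXA1125 as the active product: "AXA1125 is an orally active mixture of 5 specific AAs (leucine, isoleucine, valine, arginine, and glutamine) and Nac (an AA derivative". The text under Table 1 lists its excipients: "The excipients within AXA1125 include citric acid, soybean lecithin, xanthan gum 180, sucralose, orange flavor, custard flavor, FD&C yellow no. 6", followed by a disintegrant, silicon dioxide and magnesium stearate.

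Placebo has its own Section 5.1.2 and its own Table 2. Section 5.1.2 sets out how its excipients differ from those of AXA1125. Soybean lecithin is removed. On acidity, the section explains that "sodium citrate dihydrate has been added and the citric acid amount reduced in order to match the pH of AXA1125". On the ingredients that make up the bulk of the powder, it states that "maltodextrin and sunflower oil powder have been added as fillers". Table 2 lists "Sunflower oil powder" as a filler.

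Section 7.4.2 randomizes subjects 1:1 to AXA1125 or placebo. Section 4.4 plans about 40 subjects in Cohort A and about 10 in Cohort B.

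**The concern.** In a blinded two-product trial nobody knows at screening which product a subject will receive, so a screen for known allergies needs to cover both. Here it covers one. Someone who reports a sunflower allergy at screening meets no written exclusion, yet has a one-in-two chance of being assigned a product that contains sunflower oil powder. The subject would then take it at home twice a day, with clinic visits planned only on Days 1 and 28.

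The narrow wording does not look like a naming convention. The protocol has a term that covers both products: the synopsis entry on duration of exposure defines study drug as AXA1125 or placebo, and the second exclusion in Section 4.2 uses study drug when it refers to absorption. The allergy criterion names AXA1125 instead.

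What is at stake is subject safety in the control arm. Safety and tolerability are also stated objectives in both cohorts (Sections 2.1.2 and 2.2).

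**Working it through.** The check is a comparison of texts, with some simple arithmetic on exposure. The plan states no figure for the allergy risk itself, so there is none to reproduce.

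**1. Ingredients of the two products**

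- In placebo but not listed for AXA1125: maltodextrin, sunflower oil powder, sodium citrate dihydrate.
- In AXA1125 but not in placebo: the active ingredients and soybean lecithin.

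The AXA1125 excipient list is introduced in a way that might leave it open-ended. Section 5.1.2 settles the matter by describing the three ingredients as additions that distinguish placebo from AXA1125.

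Sodium citrate is of little substance here. AXA1125 already contains citric acid, and the footnote to Table 2 says that the placebo's total is split between the acid and its salt and matches the daily amount in AXA1125. That leaves sunflower oil powder and maltodextrin, and the documents give no sign of an allergy concern specific to maltodextrin.

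**2. Other eligibility criteria**

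No other criterion in Sections 4.1 and 4.2 names allergy or sensitivity. The last exclusion concerns attendance and ability to comply. The inclusion criterion on general health could be applied by judgement to a serious allergy, but does not name one.

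**3. Daily amount in the placebo arm**

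Inputs from Section 5.1.2: "sunflower oil powder (~21.5 kcal per sachet, or up to 129 kcal per day based on 7.38 kcal/g" and "maltodextrin (~50.4 kcal per sachet, or up to 302 kcal per day based on 3.78 kcal/g". Three sachets twice daily make 6 sachets.

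The protocol's daily calories reproduce first:

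- Sunflower oil powder: 6 × 21.5 = 129 kcal, as stated.
- Maltodextrin: 6 × 50.4 = 302.4 kcal, stated as 302.

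Grams = kcal per sachet ÷ kcal per gram × 6:

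- Sunflower oil powder: 21.5 / 7.38 = 2.91 g per sachet; × 6 = 17.5 g/day.
- Maltodextrin: 50.4 / 3.78 = 13.3 g per sachet; × 6 = 80 g/day.

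**4. Number of subjects**

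At 1:1, placebo subjects number about 40/2 + 10/2 = 20 + 5 = 25 of 50.

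Let p be the proportion of otherwise eligible subjects who have a relevant known allergy and are not screened out by the investigator. The documents do not give p. The expected number who are dosed with the ingredient is 50 × p × 0.5 = 25p. To expect even one such subject, p would have to be 1/25 = 4%.

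**The case against.** The strongest reply is that meeting the criteria does not oblige a site to enrol anyone. Under Section 4.4 a subject who meets them is considered for enrollment, and is enrolled only after also being selected and randomized. Section 4.5.1 lets the investigator stop treatment or withdraw a subject at any time for safety. The health criterion in Section 4.1 and the medical history taken at screening (Section 6.3) give further room for judgement. This stands. A reader might infer that a site following the protocol has to accept a sunflower-allergic subject; the documents do not say so. They leave the subject to discretion, which is weaker than the explicit rule that they apply to AXA1125.

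A second reply is that the gram amounts do not measure risk. They are weights of an oil powder and a carbohydrate, not of an allergen, and the documents give no allergenic content. This also stands. The figures show only that exposure is repeated and more than trace.

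A third is that the Pharmacy Manual holds further placebo details and the consent pages were not available for review, so a safeguard may exist elsewhere. That is possible, but the eligibility criterion would still be too narrow as worded.

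A reader might also infer that the gap would distort the comparison of safety between arms. Nothing in the documents supports this. It would need an allergic subject who is accepted despite the allergy, is allocated to placebo and reacts, and no figure makes that sequence likely. One event among about 20 placebo subjects in Cohort A would be 5%, and one among 5 in Cohort B would be 20%, but it would be visible in the individual listings planned in Section 7.4.6.

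**Conclusion.** The gap in wording is real, and the text alone establishes it: the criterion reaches AXA1125 only, the placebo contains sunflower oil powder and maltodextrin that AXA1125 does not, and no other written criterion covers allergy to them. Such a subject is not explicitly excluded. The conclusion assumes that the ingredient lists in Sections 5.1.1 and 5.1.2 are complete for the ingredients that differ.

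The consequence is small. The number of subjects affected cannot be computed from the documents and is probably very small in a trial of about 50. Confidence is high for the wording gap and low for any actual harm. This is a minor point and a cheap improvement.

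**What to change.** Reconcile the exclusion with the placebo composition. In the synopsis and in Section 4.2, extend the allergy criterion from ingredients of AXA1125 to ingredients of the study drug (AXA1125 or placebo). A pointer to Table 1, the excipient list beneath it and Table 2 would let sites check a reported allergy against the full list.

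The change is one phrase in two places and can go into the next amendment. Its downside is an occasional extra screen failure. No endpoint, analysis or sample-size text has to change.
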